### Measures against bias

The study is unblinded with respect to the GPs, the patients, and their caregivers. However, the assessment by telephone interview after one and two years is done by students who are not informed to which study arm the patient belongs.

From the methodological point of view, the main problem with cluster randomized trials is the potential for selection bias [50]. Although the GPs are randomly assigned to the study arms, inclusion of patients and their caregivers may be biased by foreknowledge of the allocation. This can occur because doctors may differently approach patients depending on the study arm they belong to or because patients and caregivers may differently consent to participation.

To address the problem of selection bias, we asked the participating GPs to initially provide a list of all dementia patients in their practice whom they considered eligible for the study. These lists will allow comparison of the basic characteristics of patients participating vs. those not included in the study overall and between study arms.

### Analysis

The confirmatory analysis of the study concerns the comparison of the three study groups with respect to the primary endpoint. To account for multiple testing, we plan to apply a closed testing procedure, which consists of testing the global null hypothesis of no difference between all three groups, and, in case of rejection, three subsequent pairwise comparisons with a significance level of 5%. Since the primary endpoint is a censored failure time variable, survival models adapted for clustered data will be applied [51]. All analyses will primarily be done according to the intention-to-treat approach. Analyses of secondary endpoints will use generalized linear models accounting for cluster randomization. Selection bias will be tested and adjusted for on the basis of available baseline data. For most secondary endpoints, no measurements will be available if the patient has died or moved into a nursing home. These analyses will therefore be done on the basis of all available cases. Additional analyses will be performed by applying imputation methods to those cases where patients were admitted to nursing home. In case of severely skewed distribution of cost variables, we will check the robustness of results by applying transformations or by performing bootstrap analyses.

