## Methods/Design

### Study Design and Setting

The IDA study is designed as a three-armed cluster-randomized trial. The main research hypothesis is that for dementia patients still living at home a complex intervention consisting of an initial training of GPs in evidence based diagnosis and treatment, of the provision of caregiver support groups, and of actively approaching family counselling, can prolong time to nursing home placement in comparison to usual care. In comparison to usual care (study arm A), one intervention group receives additional training of GPs in medication and non-medication based therapies for dementia, and caregivers are offered to participate in caregiver support groups (study arm B), whereas in the second intervention group actively approaching family counselling is additionally implemented (study arm C). The duration of the intervention phase is two years. However, a change of study design became necessary due to the unexpected slow recruitment of patients (18 months instead of 6 months) and the very low participation rates of caregivers in the caregiver support groups. The main focus of the study was shifted towards the comparison of groups A and C. In group B, the actively approaching family counselling was implemented after the 1-year follow-up. Thereby, patients in arm B can serve as an intermediate intervention group in the first year and as an additional full intervention group in the second year. The new study design is shown in Figure 1.

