### Sample size

For the sample size calculation, we had to consider a multiple test procedure for a three-group comparison with respect to a censored outcome variable and with allowance for a cluster effect. The calculation was based on an error probability α = 0.05 and a statistical power 1-β = 0.90 for each of the pairwise comparisons. As a clinically relevant effect we considered a difference of 15% or more in the probability a patient is still living at home after two years. The AD2000 Collaborative Group reported that 25% of the dementia patients had to be moved to a nursing home after two years [52]. This rate was used as event rate for study arm B. As deaths are counted as event we assumed a 10% point higher rate in all study arms. Under the alternative hypothesis we estimated that 50% (arm A, usual care) vs. 65% (arm B) vs. 80% (arm C) would still live at home after two years. As a result, 227 patients per arm were needed for a study with individual randomization [53]. Allowing for a cluster effect (ICC = 0.05, correction factor = 1.2) yields 272 patients per group. With further allowance for drop-out (10%) we decided to set the recruitment target at 900 patients. The change in study design reported above was considered acceptable with respect to statistical power, since a power of 75% could still be achieved for the comparison of groups A and C with a sample size as small as 120 per group if a 20% difference in event rates was assumed.

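### The redesign makes A versus C the main comparison, but the confirmatory procedure still lets it be claimed only after a three-group test that includes arm B

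*Protocol article*

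**What the plan says.** Study Design and Setting reports the redesign that followed slow recruitment and poor uptake of support groups: "The main focus of the study was shifted towards the comparison of groups A and C". It adds: "In group B, the actively approaching family counselling was implemented after the 1-year follow-up". Arm B is then meant to "serve as an intermediate intervention group in the first year and as an additional full intervention group in the second year".

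The Analysis section says: "The confirmatory analysis of the study concerns the comparison of the three study groups with respect to the primary endpoint". The closed procedure consists of "testing the global null hypothesis of no difference between all three groups, and, in case of rejection, three subsequent pairwise comparisons", the latter at 5%. The section does not rank A versus C above the other pairs, and it does not say how arm B's second-year counselling enters the two-year comparison.

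The Sample size section gives the original basis, "error probability α = 0.05 and a statistical power 1-β = 0.90 for each of the pairwise comparisons", under the alternative that "50% (arm A, usual care) vs. 65% (arm B) vs. 80% (arm C) would still live at home after two years". It then justifies the redesign by 75% power for A versus C with 120 per group and a 20-point difference. It gives no base rate or arm-B rate for that figure, and does not say whether the 75% allows for the global test or for clustering.

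**The concern.** Two parts of the same article, written after the redesign, do not fit together. One names A versus C as the comparison that matters. The other makes any A versus C claim depend on a two-degree-of-freedom test whose result also depends on arm B. If arm B lies between A and C, which is what the redesign leads one to expect, the global test is weaker than the direct comparison. A real A versus C difference can then go unclaimed.

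The redesign also changed the meaning of the other two confirmatory pairs. Over 24 months, B versus C now compares immediate with delayed counselling, and A versus B compares usual care with delayed counselling. The sample size section powered both for an arm B without counselling.

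**Working it through.** **1. The plan's own figure.** Inputs from the Sample size section: 50% versus 65% at home, α = 0.05 (two-sided assumed), power 0.90.

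n = [1.960·√(2·0.575·0.425) + 1.282·√(0.50·0.50 + 0.65·0.35)]² / 0.15² = 226.2, so 227 per arm. Then 227 × 1.2 = 272.4, and 272 / 0.9 = 302 per arm, about 907 in total against a target of 900. The original calculation reproduces.

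**2. The 75% after the redesign.** The base rate is not given; 50% versus 70% is assumed. Power of a plain two-sided test of A versus C:

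| Effective n per arm | Power |
|---|---|
| 120 (no adjustment) | 89% |
| 120 / 1.2 = 100 | 83% |
| 120 × 0.9 / 1.2 = 90 | 79% |

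A continuity correction at 90 gives 74%. None of the uncorrected figures is 75%. The gated power in step 3 at an effective 100 is close to it. The stated 75% may therefore be a gated figure or a conservative direct one, and the text does not settle which.

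**3. Cost of the gate.** Log-rank simulation, 6,000 runs per row (Monte Carlo error about 0.6 points), exponential times, follow-up cut at two years, A at 50% and C at 70%. Gated means that the three-group test and the A versus C test both reject at 5%.

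| Effective n per arm | Arm B hazard | Direct | Gated |
|---|---|---|---|
| 100 | A's in year 1, C's in year 2 | 83% | 73% |
| 100 | midway throughout | 85% | 74% |
| 100 | midway, then C's | 85% | 76% |
| 100 | equal to C | 84% | 81% |
| 120 | A's, then C's | 90% | 82% |
| 120 | equal to C | 90% | 88% |
| 90 | A's, then C's | 80% | 68% |

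The loss is about 2 to 10 points at an effective 100 to 120, and about 11 at 90 in the least favourable case. At the original rates, with B switching to C's hazard after one year and an effective 100 per arm, direct power is 99.5% and gated 99.0%.

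**4. What arm B now represents.** Exponential hazards from the stated rates, −ln(S)/2 per year: A 0.347, B 0.215, C 0.112. With C's hazard in arm B's second year, S_B(24 months) = exp(−0.215 − 0.112) = 0.721.

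- B versus C: the gap falls from 80 − 65 = 15 points to 80 − 72 = 8.
- A versus B: the gap rises from 65 − 50 = 15 points to 72 − 50 = 22.

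With 390 recruited, about 130 per arm if equal, and 130 / 1.2 = 108 effective, two-proportion power is about 27% for B versus C and 92% for A versus B.

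**The case against.** The strongest reply is that the closed procedure is sound. With three groups, a global test followed by pairwise tests at 5% controls the familywise error over all three claims. That stands: this is not a type I error problem, and the gate does not bias the A versus C estimate. The size of the loss also rests on assumed rates, and at 50/65/80% it is negligible. But the sponsor's own justification retreats to a 20-point difference, where the loss matters.

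The article post-dates the redesign, so the three-group test may have been kept on purpose. That cannot be excluded, and it would be wrong to call it an oversight. If it was deliberate, the article should justify it and give the power of the whole procedure.

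Three stronger readings are tempting, and the article does not support them.

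- A reader might infer that the 24-month arm-B contrasts are biased or meaningless. The abstract describes the intervention arms as receiving counselling from baseline or after the one-year follow-up, so both contrasts remain randomised intention-to-treat comparisons. Their target has changed; that is not bias.
- A reader might infer that the plan rests on a non-randomised second-year comparison among patients still at home at 12 months. The article says only that arm B can serve as a full intervention group then. The confirmatory endpoint runs from study entry, and no landmark analysis is made confirmatory.
- A reader might infer that the arm-B contrasts should be cut at 12 months and tested C versus B first. On the plan's rates that comparison is 89% versus 81% at home, with about 44% power at an effective 108. It would put the better-powered A versus B contrast behind a weak step.

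**Conclusion.** The point holds as an inconsistency with a moderate cost. The declared main comparison is subordinate to a test involving an arm that the redesign changed. Under 50% versus 70% at home this costs about 2 to 10 power points at an effective 100 to 120 per arm, slightly more at 90, and close to nothing at the original rates. These figures assume exponential times, equal arms and a design effect of 1.2. The arm-B contrasts remain valid, but they are not the ones that were powered: under the plan's own rates the B versus C gap roughly halves. The 75% power cannot be tied to a specific procedure.

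**What to change.** - Make A versus C on the primary endpoint over 24 months the first confirmatory test at two-sided 5%, outside the global gate.
- Test the arm-B contrasts only afterwards, in a pre-stated hierarchy or as secondary analyses, and label them as comparisons with delayed counselling.
- Label any use of arm B's second year as a full-intervention group exploratory.
- State whether the 75% refers to A versus C alone or to the full procedure, with its base rate, arm-B rate and cluster allowance.

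The cost is wording. The omnibus test is given up, and in a hierarchy the arm-B claims become conditional on A versus C. Familywise error stays at 5% under a fixed sequence. Follow-up had ended and the analysis phase had begun when the article was written, so the change must be dated and fixed before outcomes are compared by arm.

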### Sample size

For the sample size calculation, we had to consider a multiple test procedure for a three-group comparison with respect to a censored outcome variable and with allowance for a cluster effect. The calculation was based on an error probability α = 0.05 and a statistical power 1-β = 0.90 for each of the pairwise comparisons. As a clinically relevant effect we considered a difference of 15% or more in the probability a patient is still living at home after two years. The AD2000 Collaborative Group reported that 25% of the dementia patients had to be moved to a nursing home after two years [52]. This rate was used as event rate for study arm B. As deaths are counted as event we assumed a 10% point higher rate in all study arms. Under the alternative hypothesis we estimated that 50% (arm A, usual care) vs. 65% (arm B) vs. 80% (arm C) would still live at home after two years. As a result, 227 patients per arm were needed for a study with individual randomization [53]. Allowing for a cluster effect (ICC = 0.05, correction factor = 1.2) yields 272 patients per group. With further allowance for drop-out (10%) we decided to set the recruitment target at 900 patients. The change in study design reported above was considered acceptable with respect to statistical power, since a power of 75% could still be achieved for the comparison of groups A and C with a sample size as small as 120 per group if a 20% difference in event rates was assumed.

### Economic evaluation

The primary economic evaluation will be a cost-effectiveness analysis from the societal perspective. The results will be presented as incremental cost per additional year living at home. We will use the bootstrap approach to calculate confidence intervals for incremental cost-effectiveness ratios. In a secondary cost-utility analysis, quality-adjusted life years (QALYs) will be calculated based on EQ-5D values.

## Discussion

In this paper we describe the study design of an innovative cluster-randomized trial evaluating the cost-effectiveness of a complex intervention for GPs and family caregivers of patients with dementia living at home. The IDA study aims to combine several treatment options including training of GPs concerning diagnosis and treatment of dementia, out-patient specialist support for GPs, and support programs and counseling for informal caregivers of patients with dementia. The counseling for caregivers is the main intervention of the IDA study.

Particular strengths of the study design are the relatively large sample size, the cluster randomization, the long follow-up of two years, and the availability of complete health insurance data for all patients over the whole study period. Since we planned this study as a so-called pragmatic (or naturalistic) trial, we tried to aim at maximum generalizability by recruiting a large number of GPs who cover a mixed urban and rural region typical for Germany. We motivated participating GPs to include all suitable patients in the study. Formal inclusion and exclusion criteria for patients, such as availability of caregiver, were necessary and do not pose a threat to external validity. Restriction of patients to those from the AOK sickness fund seemed necessary, since we wanted to obtain complete health insurance data. This is no severe threat to external validity, since the regional AOK sickness funds have the largest share of insured patients in Germany. In 2005, about one million people or 49.6% of the population aged over 65 of the statutory health insurance market in Bavaria was insured by the AOK.

The major problem with respect to selection bias is the exclusion of patients whose caregivers are not willing to participate, either because of fear of stigmatization or other reasons. Some GPs may be more willing and able to convince patients and caregivers to participate than others, and in a cluster randomized trial this may also be related to the treatment group. In order to investigate selection bias, we plan to compare groups with respect to baseline data. In addition, we asked all GPs to initially provide a list of patients they would approach. In a subsample of about 50% of all GPs we conducted interim telephone interviews to ask them about progress of recruitment and reasons for non-inclusion.

Since patients with dementia may not be able to give correct information, we collected all data via GPs or caregivers or from the sickness fund. The only exception is assessment of quality of life, which was also collected from patients.

We chose time to nursing home referral as the primary endpoint because the main concept was to help caregivers to care for their relatives suffering from dementia as long as possible in their living environment. In a recent meta-analysis only studies were selected that reported this endpoint [16]. We discussed in detail whether death before nursing home placement should be included in the primary endpoint or count as a censoring event. Other studies often do not explicitly mention how this is handled as for instance Spijker et al 2008 [16]. It was decided to include it because this would minimize any possibility of bias and we expected to be able to accept the additional random error because of the large sample size. According to data from a population based study, median survival time is five to seven years from time of diagnosis in patients with mild or moderate dementia [54]. The outcomes nursing home placement and death can be completely assessed by AOK data. Reasons for nursing home placement may be unrelated to progress of dementia, e.g. caused by other disease or by death of a caregiver. We try to document these reasons as given by the GP and the caregiver wherever possible.

Two year follow-up was considered to be necessary in order to register enough events within the duration of the study. In our sample size calculation we expected to observe 50% events within two years based on estimations from the AD2000 study [52].

There was no additional validation of the dementia diagnosis as we decided to choose a naturalistic design. However, all participating GPs had a training unit in standardized application of the MMSE.

Physicians prescribe the drug that they consider as the right one for their patient, reflecting their knowledge of the disease, the diagnosis and the characteristics of the patient. In contrast to study arm A, GPs randomized in study arm B and C were trained in treatment of anti-dementive drugs. The aim of the training was to improve the knowledge of the physicians so that the treatment follows the guideline for GPs (Witten-Herdecke University) and the therapy recommendations of the Pharmaceutical Commission of the German Medical Association. Therefore drug treatment followed evidence-based guidelines and drugs were prescribed according to their approval. Differential drug prescription may have an additional intervention effect which cannot accurately be distinguished from the effect of the non-medical interventions. However, the prescribing pattern of the GPs in the three study arms will be known from the health insurance data and will be considered in the analysis.

To prevent intervention effects depending on the family counsellor we implemented a guideline for the counsellors. However, the process of counselling is individual and depends on many different factors such as the caregiver situation, the patients' health status, the living arrangement etc. Therefore, we cannot guarantee a unique counselling effect for all counsellors.

We experienced some specific unforeseen problems in the implementation of the study design that we were able to solve in a pragmatic way. During recruitment the question arose how to deal with caregivers who care for two people meeting the inclusion criteria. We decided that both patients could take part in the study. Questions within the telephone interview relating to the informal caregiver were only assessed once.

It was planned to recruit the primary informal caregiver of the patient that is the person who carries out the largest part of informal care. However, sometimes it was not the primary informal caregiver who signed the written consent. In those cases we refrained from contacting the primary caregiver and involved the non-primary caregiver. It might be possible, that their statements on resource use are less valid as they are not as strongly involved in the caring process as the primary informal caregiver.

Some informal caregivers preferred to answer the print version of the questionnaire. If the written questionnaires had values missing, we refrained from contacting these subjects again. Answers of the written questionnaire might differ from those of the telephone interview as caregivers have not the possibility to pose clarification questions.

The resource use of informal care is measured since it plays a substantial role in caring for patients with dementia living at home [55-59]. Omission of costs of informal care would bias cost-effectiveness against formal care in favor of informal care which seems to be free of charge [56]. Measuring the economic burden of informal care is not easy for several reasons. We decided to assess and value the time the informal caregivers spent on caring for the patient. However, sometimes it is not easy to distinguish between normal housework and informal care [60]. Furthermore, different methods are available for valuing that time [61].

However, this kind of valuation does not consider possible positive effects of care giving for the informal caregiver [62,63]. However, up to now there is no consent on how informal care should be incorporated in economic evaluation.

Due to the extension of the recruitment and intervention time the counselling will be offered to some caregivers for more than 2 years. This will allow us to analyze effects of the intervention on nursing home admission beyond the planned 2-year follow-up. Furthermore, patient and caregivers agreed to provide their health care insurance data for a period of four years after study entry which allows additional long-term analysis concerning the primary end point as well as cost from a health care perspective.

From a public health perspective the IDA trial should lead to evidence based results with regard to the community effectiveness of non-medical support measures for dementia patients and their caregivers in the primary care sector. For health policy makers it is necessary to make their decisions about financing new services based on strong knowledge about the acceptance of measures in the population and their cost-effectiveness.
